### Sample size calculation

As it is the first study investigating the effect of the MBCP on smartphone behavior in adolescents, the project team can only decide the predicted intracluster correlation with reference to other studies investigating adolescent behavioral problems. The predicted intracluster correlation of 0.01 is adopted based on studies about smoking prevention and alcohol use in adolescents [55, 56]. 20 % potential dropout/noncompliance rate is considered reasonable. Assuming a Type 1 error of 0.05 and Type II error of 0.2, a total of 240 participants (i.e. 120 in each group, 60 in each school) is required to achieve a medium effect (Cohen’s *d*) of 0.5 [57] for comparing the treatment effect between the two treatment groups and among the measurement points within groups for the three outcomes to be measured – resilience, smartphone behavior and symptoms of smartphone addiction.

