### Study design and setting

This study will be an open-label, parallel-group, cluster randomized controlled trial with repeated measurement analysis. It will pragmatically evaluate the effects of the mindfulness-based cognitive programme (MBCP) on improving adolescents’ resilience, changing their smartphone behavior and reducing smartphone addictive symptoms as compared with the control group at five measurement points (i.e. baseline (T0), one month (T1), two months (T2), three months (T3) after the programme, three months’ follow up (T4)). The study will be conducted in four primary schools in Hong Kong. The primary schools will be the unit of allocation, and individual participants will be the units of analysis. The intervention group will receive the mindfulness-based programme, and the control group will receive existing counselling services for students with emotional/behavioral problems. (i.e. treatment as usual). Data collection will be started in September 2020. Key aspects of the study design can be found in Fig. 1. We designed and reported this study protocol according to the SPIRIT2013 statement.

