### Data analysis

IBM SPSS version 23 will be used for statistical analysis. Mean and standard deviation will be reported for continuous variables, i.e. age, types of smartphone functions used and total resilience score. Frequency and percentage will be reported for nominal and ordinal variables. Cronbach’s alpha and intra-class correlation coefficients will be calculated to determine the validities and reliabilities of the two scales: the translated Smartphone Addiction Scale and the Chinese Version of Conner-Davidson Resilience Scale – 25. Independent t-test/Mann-Whitney U test will be used to compare the socio-demographic variables between intervention and control groups. Generalized Estimating Equation model will be used to verify all the hypotheses. The socio-demographic variables will be treated as co-variates to adjust the group means. Results will be reported with 95 % confidence interval. Intention-to-treat analyses will be applied to the independent and dependent variables. Missing data will be handled by replacing the missing values with the item-specific mean. Tests performed will be two-tailed with alpha value set at 0.05. Cohen’s *d*, calculated by taking the difference of the adjusted means between two comparison groups and dividing it by the pooled standard deviation, will be used to estimate the effect size of the treatment.

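### With two schools per arm, 80% power at a two-sided 5% level for d = 0.5 is not attainable on the protocol's own inputs; a test that holds 5% has about 36–40% before any covariate adjustment

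*Protocol article*

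**What the plan says.** Under Sample size calculation, the protocol article sets the error rates ("Assuming a Type 1 error of 0.05 and Type II error of 0.2") and concludes that "a total of 240 participants (i.e. 120 in each group, 60 in each school) is required to achieve a medium effect" of d = 0.5. Two further inputs are given there: "The predicted intracluster correlation of 0.01 is adopted based on studies about smoking prevention and alcohol use in adolescents", and "20 % potential dropout/noncompliance rate is considered reasonable". No formula is shown. The same power is claimed for resilience, smartphone behaviour and addictive symptoms.

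On the design, "The study will be conducted in four primary schools in Hong Kong". Randomization and blinding allocates these schools 1:1, so there are two per arm. Study design and setting makes the school the unit of allocation and the student the unit of analysis.

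On the analysis, "Tests performed will be two-tailed with alpha value set at 0.05". Data analysis names a generalized estimating equation (GEE) model with socio-demographic covariates for all hypotheses. The limitations paragraph of the Discussion acknowledges that there are only four schools and relies on the GEE to deal with the school effect. Neither place states a small-sample correction or a reference distribution.

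**The concern.** A design effect enlarges the variance to allow for similarity within schools. It does not allow for the fact that this between-school variation must itself be estimated from the trial. With four schools in two arms, 4 − 2 = 2 degrees of freedom remain for that estimate. The critical value is then 4.30 rather than 1.96, and the power attached to a given standard error falls sharply.

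Two errors of interpretation follow, depending on how the test is carried out:

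- If inference respects the number of schools, a true effect of 0.5 SD will be missed more often than not on the stated inputs. A null result could then be read as evidence of no benefit.
- If the GEE statistic is referred to large-sample critical values, the apparent power survives, but the false-positive rate rises well above 5%.

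In either case, the stated pair of 5% Type I error and 80% power does not describe the trial.

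**Working it through.** **Inputs.** From Sample size calculation: α = 0.05, power 0.80, d = 0.5 (so SD = 1), ICC = 0.01, 20% loss, 60 recruited per school and hence 0.8 × 60 = 48 analysed per school. From Randomization and blinding: k = 2 schools per arm. From Data analysis: two-tailed tests.

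**1. Reproducing 240.** Individually randomised size per arm: 2(1.96 + 0.8416)² / 0.5² = 62.8, so 63 (64 with a t correction). Design effect DE = 1 + (m − 1) × 0.01, which is 1.47 for m = 48 and 1.59 for m = 60.

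| Route | Per arm | Total |
|---|---|---|
| 63 × 1.47 / 0.8 | 116 | 232 |
| 64 × 1.47 / 0.8 | 118 | 236 |
| 63 × 1.59 × 1.2 | 121 | 242 |
| 63 × 1.59 / 0.8 | 126 | 252 |

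The stated 240 sits among these. Clustering and dropout have both been allowed for.

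**2. Normal-theory power.** SE = √(2·DE / (k·m)).

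- m = 48: √(2 × 1.47 / 96) = 0.175; 0.5 / 0.175 = 2.857; power Φ(2.857 − 1.96) = 81.5%.
- m = 60: √(2 × 1.59 / 120) = 0.163; noncentrality 3.071; power 86.7%.

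**3. The same comparison on 2 degrees of freedom.** Noncentral t, critical value 4.303:

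| Analysed per school | Power at d = 0.5 | Effect detectable with 80% power |
|---|---|---|
| 48 | 36.2% | 0.99 SD |
| 60 | 40.0% | 0.92 SD |

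A simulation of school means (400,000 replicates) gave 36.1% and 40.0%. The 95% confidence interval half-width with 48 per school is about 4.303 × 0.175 = 0.75 SD, taking the standard error at its true value.

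**4. Sensitivity to the ICC (assumed range 0 to 0.05, 48 per school).** Power is 47.1% at ICC 0 and 20.2% at ICC 0.05.

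**5. Sensitivity to baseline adjustment (assumed correlation r; ICC 0.01).** The variance is multiplied by 1 − r², assumed to apply equally within and between schools.

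| r | 48 per school | 60 per school |
|---|---|---|
| 0.5 | 44% | 49% |
| 0.8 | 69% | 74% |

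Only by stacking the two most favourable assumptions, ICC exactly 0 and r = 0.8, does the figure just pass 80%. With 48 per school the noncentrality is then 3.464 / 0.6 = 5.77 and power about 81%. That departs from the protocol's own ICC.

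**6. Where 80% comes from.** In the simulation of school means under no effect, comparing the statistic with 1.96 gave a Type I error of about 19% with an unbiased variance and about 30% with an uncorrected sandwich variance. With the unbiased variance and 48 per school, the rejection rate at d = 0.5 was about 80%. The claimed power therefore reappears, but not at a 5% level.

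**The case against.** **The 36% is not the trial's power.** A reader might infer from the table that the trial simply has 36% power. The documents do not support that. The figure belongs to an unadjusted school-level comparison at one time point with the full 20% lost. The protocol plans a covariate-adjusted GEE with a baseline and four later measurements, and its primary objective is a group-by-time interaction. The 20% also combines dropout with noncompliance; under the stated intention-to-treat approach, non-compliers need not be lost. This objection stands, and it is why the result must be given as a conditional range. It does not restore 80%: at the protocol's ICC, even an assumed baseline correlation of 0.8 leaves power at 69–74%, and the sample size section states no such correlation.

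**The 240 is not an arithmetic slip.** A reader might conclude that the number was miscalculated. It was not; it roughly reproduces. The fault lies in applying large-sample theory to four clusters.

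**The GEE deals with clustering.** It can model the correlation, but it does not supply the missing degrees of freedom. Equally, a reader might infer that the trial will run at a 19–30% false-positive rate. The article does not go that far. It is silent on the reference distribution, which may be set in an analysis plan not shown, and the simulation is a simplified one on school means. What can be said is that the claimed power depends on large-sample critical values.

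**The limitation is already acknowledged.** The Discussion mentions the four schools and hopes for larger, multisite trials. It presents the issue as possible bias that the GEE will control, and it does not qualify the power claim.

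**Conclusion.** The concern holds as a matter of power and design. On the stated inputs, the pair of two-sided 5% and 80% power for d = 0.5 is not attainable with two schools per arm. A test that holds 5% has about 36% power (48 per school) to 40% (60 per school) unadjusted, and about 44–74% across both retention levels with assumed baseline correlations of 0.5 to 0.8. The shortfall does not depend on doubting the ICC of 0.01, because the unadjusted figure with 48 per school is still 47% at ICC 0.

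The figures rest on approximately normal school means, equal school sizes, equal variances in the two arms and a between-group comparison on 2 degrees of freedom. The baseline correlations and the ICC range are assumptions, since the article gives neither. The power of the exact planned interaction test cannot be computed from what is stated.

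**What to change.** Keep the four schools and 240 students, and change the text in three places.

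1. **Sample size calculation.** Replace the 80% claim with a labelled conditional statement, for example: with two schools per arm (2 degrees of freedom) and ICC 0.01, power for d = 0.5 in an unadjusted single-time-point comparison is about 36% with 48 analysed per school and 40% with 60; the effect detectable with 80% power is about 0.99 or 0.92 SD; the 95% confidence interval half-width is about 0.75 SD with 48. Over an assumed ICC of 0 to 0.05, power with 48 per school is 47% to 20%. With baseline adjustment at an assumed correlation of 0.5 to 0.8, it is about 44–69% (48) or 49–74% (60).
2. **Data analysis and the limitations paragraph.** State that the between-group comparison uses school-level inference on 2 degrees of freedom, or a GEE with a small-sample-corrected variance and a t reference on 2 degrees of freedom. Without this, the restated power would describe a test that the protocol does not plan.
3. **Discussion.** Say that the trial is preliminary, and that a non-significant result will not be read as no effect.

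The cost is a less favourable stated power and wider intervals; no participants are added. If the sponsor prefers to keep an 80% claim, the number of schools has to rise: at ICC 0.01 unadjusted, three schools per arm give 74% (48 analysed each) or 80% (60 each), and four per arm give 92% or 95%.

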### Randomization and blinding

The four participating schools will be cluster-randomized at a ratio of 1:1 into the intervention and control groups by coin toss by the research assistant A (RA-A) who will not be involved in participant recruitment and data collection. All students recruited under the same participating school were exposed to the same intervention. The principal investigator, who will be responsible for recruiting the schools and the students, will code the participating schools with a number and a letter to represent the district and the school, respectively. RA-A will only know the four codes but not the names of the schools. The school will be assigned to the intervention group if the landed side is heads; the school will be assigned to the control group if the landed side is tails. The allocation result will be kept by the RA-A in a sealed opaque envelope until participant recruitment. The school teachers, parents and students will not be informed of the research hypotheses. RA-A will feed data into the computer in separate datasheets so that the co-investigator responsible for data analysis can analyze data without having access to information about the allocation. Hence, it is a single-blind design.

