### School and participant recruitment

Primary school will be the cluster for randomization. Four primary schools in Hong Kong will be recruited based on their eligibility and willingness to participate in the study. The inclusion criteria for school selection are: (1) it is either a local government-subsidized or a private primary school; and (2) there are currently no interventions adopted by the school to manage students’ smartphone behavior. The exclusion criteria are (1) it is an international school; and (2) there are currently interventions being implemented by the school to manage students’ smartphone behavior.

A convenience sample of 240 students will then be recruited from the selected schools (i.e., 60 students from each school) based on their eligibility and consent to participate. The inclusion criteria are: (1) adolescents are aged 10–11 years; (2) adolescents are enrolling in class level 5; (3) adolescents possess a smartphone or can access a smartphone; (4) adolescents can speak, understand and write Cantonese; (5) adolescents are cognitively capable of following simple instructions. Adolescents have intellectual/learning disabilities will be excluded from the selection.

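### Tossing a coin for each of four schools does not secure the stated 1:1 allocation: it gives two schools per arm only 37.5% of the time and leaves an arm empty 12.5% of the time

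*Protocol article*

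**What the plan says.** The Randomization and blinding section of the protocol article states both a ratio and a mechanism: "The four participating schools will be cluster-randomized at a ratio of 1:1 into the intervention and control groups by coin toss". It then defines the mechanism. On one side of the coin, "The school will be assigned to the intervention group if the landed side is heads"; on the other, "the school will be assigned to the control group if the landed side is tails". Both outcomes are defined for a single school. The section mentions no pairing of schools, no block, no point at which tossing stops, and no rule for repeating an unbalanced set of tosses. Research assistant A carries out the allocation and sees only four codes, each made up of a district number and a school letter.

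Two other places depend on equal arms. The Abstract repeats the 1:1 ratio, and the Sample size calculation states that "a total of 240 participants (i.e. 120 in each group, 60 in each school) is required". At 60 students per school, 120 per group means exactly two schools in each arm.

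**The concern.** A rule that sends each school to an arm by its own toss fixes the probability of assignment for each school, but not the number of schools per arm. With many clusters the difference would be minor. With four, it decides whether the trial has the design on which its sample size rests.

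Three things are at stake:

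- **Precision.** A 3:1 split loses power that the sample size calculation counts on.
- **Replication.** With one school in an arm, that arm carries no information on variation between schools. The Discussion relies on the generalized estimating equation model to handle the school effect, but no model can supply replication that the design lacks.
- **Integrity of the allocation.** If the tosses come out unbalanced, someone must decide what to do next. The text gives no rule, so the decision would be made without documentation at the step where the trial most needs protection from discretion.

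**Working it through.** **Inputs.** Four schools (School and participant recruitment: "Four primary schools in Hong Kong will be recruited based on their eligibility and willingness to participate in the study"); 60 students per school and 120 per group, intracluster correlation 0.01, Cohen's d 0.5, 20% dropout (Sample size calculation); error rates from the same section ("Assuming a Type 1 error of 0.05 and Type II error of 0.2"); two-sided testing (Data analysis: "Tests performed will be two-tailed with alpha value set at 0.05"). Assumed: a fair coin and one independent toss per school.

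**Step 1: reproduce the planned size.** For d = 0.5, two-sided 0.05 and power 0.80, two independent means need 63 per arm. The design effect is 1 + (60 − 1) × 0.01 = 1.59, so 63 × 1.59 = 100.2. Multiplying by 1.2 for dropout gives 120.2 per arm, which matches the stated 120. The figure therefore presumes two schools of 60 in each arm.

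**Step 2: distribution of the allocation as written.** The number of schools sent to intervention is Binomial(4, 0.5), with 2⁴ = 16 equally likely sequences.

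| Schools per arm | Students per arm | Probability |
|---|---|---|
| 2:2 | 120 and 120 | 6/16 = 37.5% |
| 3:1, either direction | 180 and 60 | 8/16 = 50% |
| 4:0, either direction | 240 and 0 | 2/16 = 12.5% |

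The planned design fails to appear with probability 10/16 = 62.5%.

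**Step 3: cost of a 3:1 split.** With equal school sizes, the variance of the arm difference is proportional to 1/a + 1/b, where a and b are the numbers of schools. The ratio of 3:1 to 2:2 is (1/3 + 1)/(1/2 + 1/2) = 1.333, an increase of 33%.

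Power by normal approximation is Φ(d/SE − 1.96), where SE² = (DE/m)(1/a + 1/b), m is the number analysed per school and DE = 1 + (m − 1) × 0.01.

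| m per school | DE | Power at 2:2 | Power at 3:1 |
|---|---|---|---|
| 48 (60 × 0.8) | 1.47 | 81.5% | 69.7% |
| 60 (no dropout) | 1.59 | 86.7% | 75.8% |

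A 3:1 split falls below the planned 80% in both cases. These powers use the plan's own intracluster correlation and treat it as known. At 4:0 no comparison can be made.

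**Step 4: the most likely informal repair.** Suppose tossing stops once an arm holds two schools and the remaining schools go to the other arm. This guarantees 2:2, but the six allocations are not equally likely. In order of tossing (I = intervention, C = control), IICC and CCII each have probability 1/2 × 1/2 = 1/4. ICIC, ICCI, CIIC and CICI each have 1/2 × 1/2 × 1/2 = 1/8. The first two schools tossed share an arm with probability 1/4 + 1/4 = 1/2, against 2/6 = 1/3 under an equal draw. The last school is always forced, and the last two are forced half the time. Order of tossing therefore matters, and none is specified. Because the codes carry the district, tossing in code order could tend to place schools from one district in the same arm.

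**The case against.** The strongest reply is that the section states the 1:1 ratio first and only then says what heads and tails mean. It does not say that the tosses are independent or that every school gets its own. One toss per pair of schools, or stopping when an arm is full, would give 2:2, and a condensed article might omit such detail. The 1:1 ratio could also be read as equal probability of assignment, which fair tosses satisfy.

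Some of this stands. The percentages describe the rule as literally written, and the intention is clearly two schools per arm. Stopping when full still gives every school probability 1/2 of intervention and favours neither arm. Its unequal allocations would matter mainly for a randomisation test, which is not the planned analysis. Repeating the whole set of four tosses until it balances would give six equally likely allocations and would be sound if specified in advance. Data collection was planned from September 2020 and the article appeared in June 2021, so allocation may already have been done.

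The rest does not rescue the text. Reading 1:1 as equal probability does not fit the fixed "120 in each group, 60 in each school". Every repair needs a rule that the article does not contain. Nor is this detail left to a fuller document: the article states a mechanism, and that mechanism does not deliver the design stated beside it.

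**Conclusion.** The concern holds. The allocation rule as written is wrong for the stated design: simple randomisation of four schools yields the planned 2:2 split only 37.5% of the time, a 3:1 split 50% of the time, and no comparison at all 12.5% of the time. These figures are exact, given a fair coin and one independent toss per school. The power loss at 3:1, about 12 percentage points with 48 completers per school, also rests on the plan's intracluster correlation of 0.01, its effect size of 0.5 and a normal approximation. If an unstated restriction was in fact used, the trial may have its two schools per arm, but the published rule does not show how. With only four clusters, allocation is the main protection against differences between schools, so this should be corrected and not left to interpretation.

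**What to change.** Replace the heads-or-tails rule with a single restricted draw: list the six ways of assigning two of the four school codes to intervention, number them 1 to 6, and have research assistant A select one with equal probability, by one die roll or by a computer random number with a recorded seed, after all four schools have been recruited and coded. This gives 2:2 with certainty, makes all six allocations equally likely, removes any dependence on the order of the codes, and fits the existing coding and sealed-envelope arrangements. It costs one sentence and nothing in sample size, analysis or conduct.

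If allocation has already been carried out, do not redraw. State instead how the tosses were made, in what order, whether any were repeated or any school was assigned without a toss, and how two schools per arm resulted.

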### Outcome measures

#### Demographics

Demographic variables will be gender, age, parents’ educational attainment, parents’ employment status, family structure, parenting skills. Age will be measured in continuous scale; the other variables will be measured in nominal/ordinal scales.

#### Smartphone behavior

Smartphone behavior will be operationalized in terms of duration of daily smartphone use and types of smartphone functions used. Duration of daily smartphone use will be assessed by one closed-ended question - ‘On average, how long do you use your smartphone on a typical day?’. The respondents will respond to the question by choosing among the six categories - ‘less than 10 minutes’, ’11–60 minutes’, ‘1–2 hours’, ‘3–4 hours’, ‘5–6 hours’, or ‘more than 6 hours’. For types of smartphone functions used, the respondents will indicate the frequency of using a specific smartphone function such as social networking, phone calls, gaming, etc. in a 5-point Likert scale (0 = never, 1 = rarely, 2 = sometimes, 3 = usually, 4 = always).

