### Hypotheses

The three primary hypotheses of this study are: (1) the smartphone behavior of adolescents can be improved by participating in a group mindfulness-based cognitive programme; (2) the smartphone addictive symptoms of adolescents can be reduced by participating in a group mindfulness-based cognitive programme; (3) the resilience of adolescents can be increased by participating in a group mindfulness-based cognitive programme. The secondary hypothesis is that socio-demographic characteristics, resilience and smartphone behavior are associated with the symptoms of smartphone addiction in adolescents.

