#### Resilience

Resilience will be measured by the Chinese Version of the Connor-Davidson Resilience Scale – 25 [58, 59]. It consists of 25 items reflecting five factors of resilience: (1) tenacity, (2) control, (3) spiritual influence, (4) positive acceptance of changes and secure relationship, and (5) tolerance of negative affect and strengthening effects of stress [58]. Each item consists of statements such as ‘able to adapt to change’, ‘close and secure relationships’, ‘sometimes fate or God can help’, ‘can deal with whatever comes’, etc. The respondents will be asked to rate their agreement with each statement based on their experiences in the previous month. If a particular situation has not arisen in that time, the respondents will be instructed to respond according to how they think they would have reacted. The respondents will be directed to indicate their response on each item with a 5-point Likert scale, 0 is ‘not true at all’ and 4 is ‘true all the time’. The total resilience score ranges from 0 to 100, with higher scores indicating greater resilience. The scale has been applied to various target populations including children 10 years old and above. A Flesch-Kincaid score of 5 indicates that the scale is expected to be understood by those with a fifth-grade level education that is 10 years of age [60]. Thus, the scale is suitable for the target group in this study. Regarding the validity and reliability of the Chinese version, the Cronbach’s alpha coefficient was 0.89. The resilience score had positive correlation with social support (*r* = 0.44) and negative correlations with depression (r=-0.38) and anxiety (r=-0.25) [59]. To ensure the scale is appropriate and comprehensible to class level 5 Hong Kong primary school students, a panel of primary school teachers will be invited to review the scale and make minor modifications in the wordings. Face validity, internal consistency and test-retest reliability will be conducted with 20 adolescents before the actual data collection.

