#### Smartphone addictive symptoms

Smartphone additive symptoms will be assessed using the Smartphone Addiction Scale-Short Version. This 10-item self-administered questionnaire was developed by Kwon et al., 2013 based on the original validated Smartphone Addiction Scale [18]. The scale addresses five domains of smartphone addiction: (1) daily-life disturbance, (2) withdrawal, (3) cyberspace-oriented relationship, (4) overuse and (5) tolerance. The respondents will rate their agreement with each item on a 6-point Likert scale, from 1 representing ‘strongly disagree’ to 6, representing ‘strongly agree’. The total addiction score possible ranges from 10 to 60. The higher the score, the more severe the addictive symptoms. The internal consistency (Cronbach’s alpha) was 0.911. Analysis of receiver operating characteristics demonstrated that for boys, the sensitivity was 0.867 and the specificity was 0.893. For girls, the sensitivity and the specificity were 0.875 and 0.886 respectively [18]. A Chinese-version of the scale will be translated based on the English version by backward translation, i.e. a native Chinese and English-speaking teacher. Face validity, internal consistency and test-retest reliability will be conducted by inviting 20 adolescents to fill out the questionnaires before actual data collection, to ensure the translated version is valid and reliable for this study.

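### The smartphone-behaviour items carry a primary hypothesis but lie outside the planned 20-adolescent reliability check, so a gross wording or category fault could reach baseline unnoticed

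*Protocol article*

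**What the plan says.** All references are to the protocol article.

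- **Hypotheses:** "The three primary hypotheses of this study are: (1) the smartphone behavior of adolescents can be improved". Sample size calculation names smartphone behaviour among the three outcomes that 240 participants are meant to cover at d = 0.5.
- **Smartphone behavior:** "Duration of daily smartphone use will be assessed by one closed-ended question". The upper categories read "1–2 hours’, ‘3–4 hours’, ‘5–6 hours’, or ‘more than 6 hours". For functions, "the respondents will indicate the frequency of using a specific smartphone function such as social networking, phone calls, gaming, etc", scored 0 to 4. The section cites no source, validity evidence or reliability figure.
- **Resilience:** cites the scale, gives a Cronbach's alpha of 0.89, plans a teacher panel to review the wording, and states "Face validity, internal consistency and test-retest reliability will be conducted with 20 adolescents before the actual data collection".
- **Smartphone addictive symptoms:** cites the scale, gives an alpha of 0.911, and states "Face validity, internal consistency and test-retest reliability will be conducted by inviting 20 adolescents to fill out the questionnaires before actual data collection". The purpose given is to show that the translated version works in this study.
- **Data analysis:** alpha and intraclass coefficients "will be calculated to determine the validities and reliabilities of the two scales", which the sentence then names as the addiction and resilience scales.

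**The concern.** Of the three primary measures, the one with the least stated support is the only one for which no check before data collection is described. The plan accepts that pupils aged 10–11 may misread an instrument and arranges a check for the other two. The same pupils must recall and average their daily phone use, and rate how often they use each function, on items that get no such check.

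Two things are at stake. First, a wording or category fault is cheap to mend before T0. Once T0 has been collected, a change would break comparability across T0 to T4. Second, if hypothesis 1 shows no effect, a reader will ask whether the programme did nothing or the item was too noisy to show it, and the plan sets up no reliability figure for these items to help answer that.

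**Working it through.** **1. Coverage of the three primary measures**

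| Measure | Source cited | Reliability given | Check in 20 adolescents described | Covered by the coefficients in Data analysis |
|---|---|---|---|---|
| Resilience | yes | alpha 0.89 | yes | yes |
| Addictive symptoms | yes | alpha 0.911 | yes | yes |
| Smartphone behaviour | no | none | no | no |

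The last column matters most. A condensed article may well omit the source of simple usage items. Here, however, Data analysis states the scope of the reliability work and lists two scales.

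**2. Duration categories**

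The six options are under 10 minutes, 11–60 minutes, 1–2 hours, 3–4 hours, 5–6 hours and over 6 hours. Read literally, 2.5 hours and 4.5 hours have no option, nor does anything from 10 minutes up to 11. Sixty minutes fits two options. A child who rounds to whole hours can still answer, but may round differently at different waves. A face-validity check could bring this out.

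**3. The plan's own sample size**

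Inputs from Sample size calculation: d = 0.5, type I error 0.05 (two-tailed per Data analysis), power 0.80, ICC 0.01, 60 per school, 20% dropout.

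- Unclustered n per arm = 2 × ((1.960 + 0.842)/0.5)² = 62.8
- Design effect = 1 + (60 − 1) × 0.01 = 1.59, giving 62.8 × 1.59 = 99.8
- Dropout: 99.8 × 1.2 = 119.8, so 120 per arm and 240 in total

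The stated figure reproduces. Dividing by 0.8 for dropout instead would give 250.

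**4. What measurement noise would do, under one assumption**

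Assume that 0.5 is the standardised effect free of measurement error. The observed effect is then 0.5 × √reliability. Completers per arm are 120 × 0.8 = 96, or 48 per school. The design effect is 1 + 47 × 0.01 = 1.47, and the effective n is 96/1.47 = 65.3. Power = Φ(d × √(65.3/2) − 1.96). The document gives no reliability for these items, so it is assumed over a range.

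| Assumed reliability | Observed d | Power |
|---|---|---|
| 1.0 | 0.50 | 81.5% |
| 0.8 | 0.45 | 72% |
| 0.7 | 0.42 | 67% |
| 0.6 | 0.39 | 60% |
| 0.5 | 0.35 | 52% |

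This is a two-mean calculation at one time point. It is not the planned GEE analysis of an ordinal item over five waves, and it ignores the small number of schools, which is a separate matter.

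**5. What 20 adolescents can show**

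By Fisher's z with standard error 1/√17, an observed test-retest coefficient of 0.7 has an approximate 95% interval of 0.37 to 0.87. With a cut-off of 0.6, an item whose true value is 0.7 would fall below it about 24% of the time, and an item at 0.5 would pass about 28% of the time. The pilot can reveal gross faults but cannot grade items.

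**The case against.** **The power figures.** Data analysis defines Cohen's d as the adjusted mean difference over the pooled SD, that is, the SD of scores as measured. Noise is already in that SD, so if the observed d is 0.5, power is unchanged whatever the reliability. The same shrinkage applied to the two published alphas would give about 77% and 78%, so it does not single out this outcome. This stands. A reader might infer from the table that hypothesis 1 is underpowered, but the document does not support that. The table is a conditional illustration.

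**The pilot's focus.** A reader might say that the pilot is spent on scales already shown to be reliable. That is not so. The addiction scale is to be newly translated and the resilience wording may be modified, so the published alphas do not cover the versions to be used. Piloting them is sound.

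**Whether the items are really left out.** The addiction-scale section has the 20 adolescents complete questionnaires, in the plural, which could mean the whole booklet. The purpose stated in that sentence is the translated scale, and Data analysis names two scales, so exclusion is the better reading. It remains a reading. Alpha cannot apply to a single item in any case, but face validity and test-retest agreement can.

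**Evidence available later.** All outcomes are collected at T0 to T4, so the control group's repeated answers give some indirect evidence of stability. This stands. It rules out calling a null result uninterpretable, but it comes too late to mend the wording.

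**Conclusion.** The point holds as a cheap improvement to a primary measure. The items behind hypothesis 1 have no stated source or reliability, and the described reliability work does not extend to them. A gross fault could reach T0 unseen, and the gaps at 2–3 hours and 4–5 hours show that this is a concrete risk. A null result on hypothesis 1 would be ambiguous between no effect and measurement noise.

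No size can be put on a power loss. The fall from 81.5% to between 72% and 52% holds only if 0.5 is the error-free effect and reliability lies between 0.8 and 0.5, neither of which the document states. Nothing here invalidates the trial or its other two primary outcomes. The conclusion rests on reading the 20-adolescent check as confined to the two named scales.

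**What to change.** Extend Smartphone behavior and Data analysis as follows.

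1. The same 20 pilot adolescents answer the duration item and every function rating at both test-retest sittings, with a face-validity check. Report a weighted kappa or intraclass coefficient for each item with its confidence interval.
2. Before T0, correct any item that children misunderstand, or that shows gross disagreement or gaps between categories. Set no fixed kappa cut-off, given n = 20. The duration categories can be made contiguous and non-overlapping now.
3. Beside the hypothesis 1 result, report control-arm T0–T1 agreement on these items, using observed answers only. Treat it as an approximate lower bound on reliability, because true change over the four weeks also lowers agreement.

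The cost is a few extra pilot minutes, a few sentences in the protocol and possibly a wording edit before T0. Step 3 uses data already planned. Formally retesting a reworded item would need further sittings, and this fix does not ask for that. The limit is that 20 adolescents will expose gross faults only.
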